## Abstract

**Background:**

Due to continuous advances in intensive care technology and neurosurgical procedures, the number of survivors from severe acquired brain injuries (sABIs) has increased considerably, raising several delicate ethical issues. The heterogeneity and complex nature of the neurological damage of sABIs make the detection of predictive factors of a better outcome very challenging. Identifying the profile of those patients with better prospects of recovery will facilitate clinical and family choices and allow to personalize rehabilitation. This paper describes a multicenter prospective study protocol, to investigate outcomes and baseline predictors or biomarkers of functional recovery, on a large Italian cohort of sABI survivors undergoing postacute rehabilitation.

**Methods:**

All patients with a diagnosis of sABI admitted to four intensive rehabilitation units (IRUs) within 4 months from the acute event, aged above 18, and providing informed consent, will be enrolled. No additional exclusion criteria will be considered. Measures will be taken at admission (T0), at three (T1) and 6 months (T2) from T0, and follow-up at 12 and 24 months from onset, including clinical and functional data, neurophysiological results, and analysis of neurogenetic biomarkers.

**Statistics:**

Advanced machine learning algorithms will be cross validated to achieve data-driven prediction models. To assess the clinical applicability of the solutions obtained, the prediction of recovery milestones will be compared to the evaluation of a multiprofessional, interdisciplinary rehabilitation team, performed within 2 weeks from admission.

**Discussion:**

Identifying the profiles of patients with a favorable prognosis would allow customization of rehabilitation strategies, to provide accurate information to the caregivers and, possibly, to optimize rehabilitation outcomes.

**Conclusions:**

The application and validation of machine learning algorithms on a comprehensive pool of clinical, genetic, and neurophysiological data can pave the way toward the implementation of tools in support of the clinical prognosis for the rehabilitation pathways of patients after sABI.

## Introduction

Severe acquired brain injury (sABI) is characterized by traumatic, anoxic, vascular, or other brain damages that cause coma for at least 24 hand frequently lead to permanent sensorial, motor, cognitive, or behavioral disabilities. The incidence rate of sABI patients is estimated between 10 and 15 new cases/100,000 persons/year and the prevalence rate between 300 and 800 cases /100,000 persons, which represents comprehensively about 150,000 persons in 2016 in Italy (1, 2).

After sABI, some patients may survive in a state of prolonged disorder of consciousness (DoC) (3), a condition that encompasses (1) unresponsive wakefulness syndrome (UWS), in which the eyes are open, but there is no evidence of voluntary behaviors and (2) minimal consciousness state (MCS), an intermediate state in which minimal, inconsistent but reproducible behavioral signs of responsiveness are present (4). Based on the complexity of patients' behavioral responses, a subcategorization of MCS patients was proposed (5); namely, “MCS minus” (MCS–) characterizes patients with intentional low-level behavior, such as visual search or localized motor response to nociceptive stimulus, and “MCS plus” (MCS+) indicates patients with high-level behavioral interactions, such as execution of simple verbal commands (5). In some cases, patients recover full consciousness, as marked by the regaining of functional and reliable “yes/no” communication (emergence from MCS, E-MCS), but they may still present severe motor and cognitive or behavioral impairments persisting lifelong.

Besides the severity of the neurological state, patients with sABI frequently present a high clinical complexity characterized by very frequent comorbidities (6) and medical complications (7), which can further impact clinical improvement and survival. Although late consciousness recovery and progression have been reported in patients with UWS or MCS (8), long-term mortality is high (42–52%) in patients with prolonged DoC (1, 2), and survivors frequently show severe to extremely severe outcomes (9).

Younger age, shorter postevent time, and traumatic etiology have been identified as the possible clinical predictors of short-term consciousness recovery in patients with prolonged DoC (10).

On the other hand, only a few studies have investigated the clinical conditions in patients with prolonged DoC in the long term (8, 9, 11). As the evidence about functional and clinical conditions of these patients in the middle- and long-term is limited, a consensus about solid predictors of recovery is still missing.

More recently, a higher total score on the Coma Recovery Scale-revised (CRS-R) at admission in the intensive rehabilitation unit (IRU) and the progression of this score during the first 4 weeks of hospitalization have been identified as prognostic factors for consciousness or responsiveness recovery in the medium-term (12, 13). Moreover, for what concerns quantitative measures, the bilateral absence of cortical (N20) components of somatosensory-evoked potentials (SEPs) is considered the most accurate neurophysiological marker for an unfavorable prognosis of consciousness improvement with high specificity, especially in the postanoxic etiology of DoC, for both short- (14) and long-term prognoses (15, 16). Further, visual analysis of conventional EEG background activity and reactivity collected upon admission to the IRU was recently identified as a possible predictive marker for a better evolution of consciousness at discharge (17–19) or 6 months after brain injury (20). Additional factors have been reported to be prospectively associated with motor improvement in sABI patients who recovered consciousness: the evaluation of residual central neural motor circuit and the analysis of motor-evoked potential (MEP) may increase prognostic accuracy for motor limb recovery and thus improve the functional prognosis in brain-damaged patients (21). Further, the presence of critical illness neuromyopathy (CINMP), diagnosed by electromyography at the IRU admission, has been reported to associate with a lower functional outcome at discharge (18, 22).

Additionally, the influence of genetic and environmental (epigenetic) factors on the outcome of severe traumatic brain injuries (23) is also studied in the literature. New prognostic information was provided on acquired brain lesions by the analysis of different genes, such as those encoding apolipoprotein E (ApoE), catechol-O-methyltransferase (COMT), and brain-derived neurotrophic factors (BDNFs) (24). Expression of different ApoE protein isoforms (E2, E3, E4) affects lipoprotein complexes associated with LDL receptors. Based on this, ApoE is essential for the normal catabolism of triglyceride-rich lipoprotein constituents, and the different ApoE isoforms have a deep effect on peripheral lipid metabolism. ApoE, in the brain, acts as a scaffold with the formation of HDL particles, which promote the proteolytic degradation of soluble forms of amyloid-beta; therefore, ApoE may be of interest in understanding the impact of genetics on the long-term outcome of sABI patients (25). BDNF is a member of the nerve growth factor family synthesized by neurons and expressed by different brain regions, including the cortex and hippocampus, acting to modulate synaptic connections and to form new synaptic contacts. There is a functional single-nucleotide sequence polymorphism changing valine to methionine at codon 66 that has been associated with memory impairment in neurodegenerative disease (26). Given these premises, an accurate and comprehensive characterization of patients after sABI, with or without DoC, should include neuronal damage, potential neuroplasticity, and neurofunctional, and clinical status. A comprehensive assessment of individual patients' profiles and the identification of predictive markers could allow the planning of personalized rehabilitation and treatment pathways, based on solid prognostic information.

This paper describes the background and methods of an Italian multicenter study that will prospectively investigate outcomes and baseline predictors or biomarkers of functional recovery in a large cohort of patients with sABI admitted to postacute inpatient rehabilitation. The study aims to identify clinical and functional factors, neurophysiological patterns, and genetic polymorphisms which may predict short- and long-term functional recovery and, possibly, support the clinicians in optimizing rehabilitation outcomes by the development of personalized strategies. For this purpose, patients will be assessed at IRU admission, at 3 months from IRU admission, and in the chronic phase (i.e., until 24 months from the acute event).

## Methods and Analysis

### Study Design and Participants

The proposed study is a longitudinal multicenter observational cohort study, including four IRUs of the Fondazione Don Carlo Gnocchi Institute (FDG) located in Northern (Milano, La Spezia), Central (Firenze) and Southern Italy (Sant'Angelo dei Lombardi) of the Fondazione Don Carlo Gnocchi Institute (FDG). The study was registered on ClinicalTrials.gov with the following registration number: NCT04495192.

Patients with sABI admitted in the above-mentioned IRUs and fulfilling the following inclusion criteria will be consecutively enrolled.

Inclusion criteria were as follows:

time from sABI < 4 monthsage >18 yearswritten informed consent.

No additional exclusion criteria, other than the absence of a signed informed consent or age and time from onset out of range, will be considered.

The sample size estimation was based on the functional recovery assessed by GOS-E as the outcome. Based on the average number of sABI patients referring to the four IRUs involved in the study in the previous years, we estimate 36 months to enroll 520 patients.

In particular, UWS and MCS sample size was dimensioned separately building on the literature findings that show a favorable outcome [GOS-E>4, (4, 5)] in 3% and 47% of cases, respectively (27). Uncertainty of an additional 3–5% respectively on those values was considered. Assuming a level of significance of 0.05, a sample of 384 patients for the MCS group and 125 for the UWS group was achieved. Based on the average number of sABI patients referring to the four IRUs involved in the study in the previous years, the sample was assigned to each center (200 from Firenze and Milano, 60 from La Spezia and Sant'Angelo dei Lombardi).

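### The 520 total leaves 11 places (2.1%) beyond the 384 MCS and 125 UWS patients for every conscious entrant and every missing GOS-E, so the planned precision of about ±5 and ±3 points is not secured

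*Protocol article*

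**What the plan says.** All the sample-size statements are in the Protocol article, Study Design and Participants. GOS-E is the outcome used for sizing, and UWS and MCS are dimensioned separately. The favourable-outcome rates taken from the literature are 3% for UWS and 47% for MCS. On precision the text says "Uncertainty of an additional 3–5% respectively on those values was considered". It continues "Assuming a level of significance of 0.05" and concludes that "a sample of 384 patients for the MCS group and 125 for the UWS group was achieved".

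The total comes from a different source, the units' past volume of sABI admissions: "we estimate 36 months to enroll 520 patients". It is divided by centre ("200 from Firenze and Milano, 60 from La Spezia and Sant'Angelo dei Lombardi"). No quota by state of consciousness is given.

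Entry is wider than the two sized groups. The Abstract (Methods) enrols "All patients with a diagnosis of sABI admitted to four intensive rehabilitation units (IRUs) within 4 months from the acute event", subject only to age and consent. The inclusion criteria in the main text contain no consciousness criterion, and enrolment is consecutive. The Introduction calls for "an accurate and comprehensive characterization of patients after sABI, with or without DoC". Under Outcome Measures, the primary outcome is assessed at T1, T2, T3 and T4, the last at 24 months from the acute event. No allowance for loss is stated.

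**The concern.** The total is almost exactly the sum of the two group sizes, yet it counts a broader population. Each patient already conscious at admission, and each GOS-E not obtained, takes a place that the precision calculation assigns to MCS or UWS. With no quota by consciousness state, nothing in the enrolment rule steers the sample towards 384 and 125.

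This is the only sample-size justification in the article. What is at stake is whether the precision behind the group sizes is a property of the cohort that will actually be enrolled. A second, smaller question is whether the UWS figure is sound even at its full size, since a 3% rate in 125 patients yields very few events.

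**Working it through.** **Inputs from the document** (Study Design and Participants): p = 0.03 (UWS) and 0.47 (MCS); d = 0.03 and 0.05 respectively; significance level 0.05; group sizes 125 and 384; total 520. Reading d as a two-sided half-width is an inference, and step 1 supports it.

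**1. Reproducing the stated sizes.** Single-proportion precision formula: n = 1.96² × p(1−p) / d².
- UWS: 1.96² × 0.03 × 0.97 / 0.03² = 124.2, rounded up to 125. This matches.
- MCS: 1.96² × 0.47 × 0.53 / 0.05² = 382.8, rounded up to 383; with p = 0.50 the result is 384.15. This agrees with the stated 384.
- A one-sided level gives 88 and 270. Swapping the two precisions gives 45 and 1064. Neither reproduces the plan.

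**2. Slack in the groups.** Half-width = 1.96 × √(p(1−p)/n). At n = 384 it is 4.99 points and at n = 125 it is 2.99 points. Both sizes are effectively minima.

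**3. Slack in the total.** 384 + 125 = 509. The centres give 2 × 200 + 2 × 60 = 520. 520 − 509 = 11, and 11/520 = 2.1%. To reach 384 MCS, 384/520 = 74% of all enrolled patients must be in MCS.

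**4. Precision at 520.** Let c be the share of patients in neither UWS nor MCS at admission, and l the share with GOS-E missing. The document gives neither, so both are assumptions. The 384:125 ratio is kept: MCS n = 520(1−c)(1−l) × 384/509, and UWS n likewise with 125/509.

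| c | l | MCS n | UWS n | MCS half-width | UWS half-width |
|---|---|---|---|---|---|
| 0 | 0 | 392 | 128 | ±4.9 | ±3.0 |
| 10% | 0 | 353 | 115 | ±5.2 | ±3.1 |
| 10% | 10% | 318 | 103 | ±5.5 | ±3.3 |
| 20% | 10% | 282 | 92 | ±5.8 | ±3.5 |
| 30% | 20% | 220 | 72 | ±6.6 | ±4.0 |

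The UWS column uses the same normal approximation as the plan, for comparability.

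**5. Chance variation in the mix.** Take c = 0 and l = 0. Both minima are met only if UWS numbers between 125 and 520 − 384 = 136. If each consecutive admission is UWS with probability 125/509, the binomial probability of 125 to 136 in 520 is about 0.44.

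**6. The UWS interval at the full 125.** Expected events are 125 × 0.03 = 3.75. The normal-approximation interval around 3% runs from 0 to 6%. Its exact coverage at p = 0.03 and n = 125, found by summing the binomial probabilities of the counts whose interval contains 3%, is 0.887. With 4 events in 125 (3.2%), the Wilson interval is 1.3% to 7.9% and the exact interval 0.9% to 8.0%. The Wilson upper arm is 7.9 − 3.2 = about 4.7 points, not 3.

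**The case against.** **The arithmetic does not exclude the plan.** A reader might infer that 520 cannot hold the two groups, or that the precision will certainly fail. The document does not support that. 509 fits within 520, and with no conscious entrants, no loss and the planned ratio the result is ±4.9/±3.0. A shortfall needs a mix or a loss rate that the document does not give. This objection stands, and the point is limited to precision that is not secured.

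**The planners may have expected mainly patients with disorders of consciousness at T0.** Motor-evoked potentials are to be recorded at rest on account of low consciousness, and several cognitive and behavioural scales have no T0 entry in Table 1. That is a fair argument against assuming a large conscious share. It fixes no figure, however, and conscious patients remain eligible.

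**Loss differs by time point.** Missing data up to 24 months bears fully only on T4. This stands. Nor should the 42–52% long-term mortality quoted in the Introduction be read as loss: if death is scored as unfavourable, it does not reduce n.

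**The UWS ±3 points is a planning input, not a promised reporting interval.** The article does not commit to normal-approximation intervals, and the reporting method may belong in the analysis plan. That is fair, but the group size of 125 rests on this approximation, and at that size it does not give 3 points at 95% confidence.

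**Few UWS events might suggest that a planned model fails.** The Statistical Analysis section states no separate GOS-E model in UWS, so nothing planned breaks. Nor is the count bound to be 4 or fewer: at 3%, 5 or more events has probability about 0.32.

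**The aim is prediction, not estimation of proportions.** True, so the effect on the stated analyses is limited. The article nevertheless chose precision of these proportions as its basis for size.

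**Conclusion.** The concern holds in a limited form. The group sizes follow from the stated inputs, but the total does not secure them. Eleven places (2.1%) must cover every conscious entrant and every missing GOS-E, and enrolment is consecutive without a quota by consciousness state. Even in the most favourable case, with no conscious patients, no loss and a true mix of 384:125, both minima are met with probability only about 0.44, although a narrow miss would cost little precision.

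The size of the effect is moderate and conditional. Over the assumed ranges (conscious share 10% to 30%, loss 0 to 20%) the half-widths run from ±5.2 to ±6.6 points for MCS and from ±3.1 to ±4.0 for UWS. These depend on assumed shares and on keeping the planned ratio; the document supplies no values from which to choose among them.

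The UWS part needs no assumption about mix or loss. At the plan's own 3% and 125 patients, the normal approximation covers about 89%, and a realistic interval is about 1% to 8%.

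**What to change.** Keep 520 and correct what is said about it in Study Design and Participants:

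- State that 520 is the total of consecutive sABI admissions, not the sum of the two sized groups plus a margin.
- Give the expected UWS, MCS and conscious split. The article already bases the 520 on the four units' past admissions, so the split should be obtainable from the same records. Give the expected share of missing GOS-E by time point, and say how deaths are counted.
- Restate the half-widths that 520 delivers under that mix and loss, in place of roughly ±5 and ±3 points.
- For UWS, replace ±3 points with a Wilson or exact interval: about 1% to 8% at n = 125, wider if fewer are expected.

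The cost is a change of wording and a look at past admission counts, with no extra patients. The downside is that the stated precision becomes less favourable.

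### The sample is justified only by 384 MCS and 125 UWS patients (509 of 520), but enrolment takes sABI admissions in any state of consciousness, so the design does not secure either group size

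*Protocol article*

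**What the plan says.** The sample-size paragraph of the Protocol article (Study Design and Participants) treats UWS and MCS separately. It takes from the literature "a favorable outcome [GOS-E>4, (4, 5)] in 3% and 47% of cases, respectively", UWS first and MCS second. It then adds a tolerance: "Uncertainty of an additional 3–5% respectively on those values was considered". With "Assuming a level of significance of 0.05", the result is "a sample of 384 patients for the MCS group and 125 for the UWS group was achieved".

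For the total, the same section says "we estimate 36 months to enroll 520 patients". It bases this on the average number of sABI patients seen at the four units in earlier years. The centre allocation is derived in the same way: "200 from Firenze and Milano, 60 from La Spezia and Sant'Angelo dei Lombardi".

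Eligibility rests on age, time from the event and consent, and enrolment is consecutive. The Abstract puts it briefly: "No additional exclusion criteria will be considered". No criterion or quota concerns the state of consciousness. The Introduction calls for "an accurate and comprehensive characterization of patients after sABI, with or without DoC". No conscious group is sized, and no expected share of conscious admissions is given.

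**The concern.** The two halves of the paragraph describe different populations. The group sizes concern patients with a DoC only. The total, the centre allocation and the accrual time concern all sABI patients. The figures agree only if about 98% of consecutive admissions are in UWS or MCS, and the article nowhere says so.

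This is the only justification given for the sample size. A reader will take 384, 125 and the two margins as what 520 patients deliver. If the case mix differs, the group sizes and margins are less favourable than stated. If instead 509 patients with a DoC were intended, the total and the 36 months are understated.

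**Working it through.** **Inputs** (all from Study Design and Participants): favourable outcome 3% in UWS and 47% in MCS; tolerance 3 and 5 points, read as the half-width of a confidence interval; significance level 0.05, taken as two-sided, so z = 1.96; groups of 384 and 125; total 520.

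**Step 1: reproduce the group sizes.** Use the one-sample precision formula n = z² p(1 − p) / d².

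- MCS: 1.96² × 0.47 × 0.53 / 0.05² = 382.8, against 384 stated (p = 0.50 would give 384.1).
- UWS: 1.96² × 0.03 × 0.97 / 0.03² = 124.2, rounded up to 125, as stated.

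A one-sided z gives 269.6 and 87.5. Exchanging the two tolerances gives 1,063.2 and 44.7. Neither fits, so the reading above is the right one. Going back from the stated sizes, the half-width z√(p(1 − p)/n) is 4.99 points at n = 384 and 2.99 points at n = 125. Neither group has slack.

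**Step 2: compare with the total.**

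- 384 + 125 = 509.
- 200 + 200 + 60 + 60 = 520, which matches the stated total.
- 520 − 509 = 11, and 11/520 = 2.1%.

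With 12 or more conscious patients, at most 508 places remain for MCS and UWS together, so at least one group falls short. This needs no assumption about the mix.

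**Step 3: no quota by state.** Even with no conscious patients, both targets are met only if UWS numbers lie between 125 and 520 − 384 = 136, that is 24.0% to 26.2% of admissions. Consecutive enrolment does not control this.

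**Step 4: size of the effect.** The conscious share c is not in the document, so the values below are assumptions. Keeping the planned mix:

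- n(MCS) = 520(1 − c) × 384/509
- n(UWS) = 520(1 − c) × 125/509
- margins from z√(p(1 − p)/n)
- total enrolment needed for 509 DoC patients = 509/(1 − c), rounded up

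| Assumed conscious share | MCS / UWS among 520 | Margins, MCS / UWS (points) | Total needed for 509 DoC |
|---|---|---|---|
| 10% | 353 / 115 | ±5.2 / ±3.1 | 566 |
| 20% | 314 / 102 | ±5.5 / ±3.3 | 637 |
| 30% | 275 / 89 | ±5.9 / ±3.5 | 728 |
| 50% | 196 / 64 | ±7.0 / ±4.2 | 1,018 |

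At the planned rate of 520 in 36 months, the last column corresponds to 36 × total/520, or about 39, 44, 50 and 70 months. These times matter only if 509 DoC patients are really required.

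**The case against.** **The figures are not miscalculated.** Both group sizes follow from the stated inputs and the centre numbers add up. This stands. The fault lies in how the two groups relate to the total.

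**A reader might infer that the sample cannot deliver the stated sizes.** The document does not support that, because it gives no share of conscious admissions. Some text suggests a cohort mainly in DoC at admission. The motor-evoked potential section has stimuli given at rest on account of low consciousness, and Table 1 starts the orientation, apathy, agitation and communication scales only at T1. Other text treats conscious patients as part of the cohort. The Introduction speaks of patients with or without DoC. The Clinical Evaluation section chooses the pain scale by level of consciousness, and Table 1 schedules it from baseline. The Discussion describes sABI survivors as including those with DoC. So the shortfall is conditional on more than 11 conscious patients, and the 10% to 50% range is an assumption.

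**A reader might also charge losses over 24 months against the 11 spare places.** That does not hold here. A loss allowance may sit in the full protocol, which is not shown. The margins are not tied to the 24-month assessment, since Outcome Measures lists T1 to T4. The 42–52% long-term mortality in the Introduction is not dropout: a death can be counted as not reaching GOS-E>4 and then stays in the denominator.

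**The consequences are limited.** Statistical Analysis plans regression and machine-learning prediction. It states no test or decision rule that uses the two margins, and conscious patients also contribute to the GOS-E models. This stands and lowers the severity.

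**Conclusion.** The point holds as a mismatch between the justification of the sample and the population enrolled. The groups of 384 and 125 take up 509 of 520 places, while the 520 are sABI admissions without regard to consciousness. The stated sizes and margins are therefore not secured by the design, and more than 11 conscious patients (2.1%) puts at least one group below its size.

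The effect on precision is small at a low conscious share and larger at a high one, as the table shows. Those margins assume the planned 384:125 mix and an outcome known for every patient. Severity is moderate: the stated precision needs correcting, but the planned prediction analyses do not rest on it.

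**What to change.** In Study Design and Participants, use the admission data that already produced the 520 to state how many UWS, MCS and conscious patients are expected among them. Then restate the two group sizes and the margins they give, and name the margins as confidence-interval half-widths.

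If 509 was meant as DoC patients only, say so, reconcile this with the eligibility criteria and the referral basis, and restate the total and the accrual time.

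The first option costs a rewording of one paragraph. It needs no extra patients, and the stated precision becomes somewhat less favourable. The second option means a larger total and longer accrual wherever the conscious share exceeds 2.1%.
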